**Withdrawal criteria**
• Participant's withdrawal of informed consent • Noncompliance with consuming the study foods

*FBG, fasting blood glucose; IFG, impaired fasting glucose; PG, postprandial glucose; IGT, impaired glucose tolerance*.

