### Intervention

This study consists of a baseline blood glucose assessment day (D2) under habitual diet conditions (before the start of the intervention, V1), two intervention periods under two different diet patterns with equal experimental days (D3-D6, D10-D13), and a standard balanced meal run-in period between the two intervention periods (D7-D9). A 3-day experiment run-in period will be set before Visit 1 (V1). During this period, all subjects will be asked to maintain their habitual eating without energy restrictions and maintain a regular daily schedule. In addition, they will not be allowed to smoke, drink, or perform vigorous exercise in the course of this trial. All subjects will wear continuous glucose monitoring (CGM) to monitor dynamic interstitial glucose in the mornings of V1. The first intervention period will be under the habitual diet condition from D3 to D6 (4 days), during which all subjects will be asked to maintain their habitual eating and daily activities, similar to the experimental run-in period. After the first intervention period, a 3-day standard balanced meal run-in period from D7 to D9 will be performed before the second intervention to ensure that the standard meals are tolerable to the individual participants. The second intervention will consist of prelunch snacks with standard meals that had the same macronutrient composition as those in the run-in period. Screening will be finished within 1 week before the experiment (V0). Randomization will be performed after the completion of screening. Outcomes will be assessed after the two intervention periods. Blood samples will be taken before and after the two intervention periods (V1-V4), and interstitial glucose will be monitored throughout the 2 week experimental period. An overview of the study visits is presented in Table 2. During the entire period of this experiment, subjects will be asked to complete a food recording diary (online) including the type, amount, and time of all meals, snacks, and drinks except water (in the form of photos and text). Subjects will be supervised daily by the researcher in charge to ensure their food diaries are uploaded on time. Physical activity and sleep will also be recorded via a mobile app for step count and sleep time records.

**Table 2 T2:** Overview of study visits.

**Visit**	**V0**	**V1**	**V2**	**V3**	**V4**
Time from the start of wearing CGM^a^	−7	1	7	10	14

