### Test snacks

In the 3 premeal snack arms, all participants will be given prelunch snacks 30 min before lunch. Prelunch snacks will comprise soy powder and milk powder which will be completely dissolved in 250 ml of water, unsalted roast whole almonds snacks with 250 ml of water, while an equal amount of water (250 ml) will be given to subjects in the control group. The total calories of the three snacks will be similar to each other, from 80 to 90 kcal. This calorie selection was based on the minimum calories needed to relieve the symptoms of hypoglycemia (28). The specific composition of the three food items is shown in Table 3.

**Table 3 T3:** Macronutrient composition of the test snacks.

**Per serving**	**Soy powder**	**Milk powder**	**Almonds**
Weight(g)	18	25	13
Energy (kcal)	83	90	85
Carbohydrate (g, % of energy)	6.2 (30%)	14.0 (62%)	2.7 (12%)
Protein (g, % of energy)	7.2 (35%)	7.5 (33%)	2.7 (12%)
Fat (g, % of energy)	3.0 (32%)	0.38 (3%)	6.8 (72%)

*As an example for soy powder, in this trial, we used a total weight of 18 grams of soy powder as a pre-meal snack, which provided 83 kcal of total energy; of the 18 grams of soy flour, 6.2 g of carbohydrates provided 30% of the total energy, 7.2 g of protein provided 35% of the total energy, and 3.0 grams of lipids provided 32% of the total energy, respectively*.

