### Standard balanced meals run-in period

A 3day run-in period will be scheduled between Visit 2 (V2) and Visit 3 (V3), during which subjects will be asked to maintain the same levels of rest and physical activity as they did during the experimental period. Subjects will be given standard balanced meals 3 times per day during the run-in period and will not be provided with premeal snacks. Furthermore, researchers will train the subjects to eat in the same fixed meal order and have a similar duration of each meal (to keep a similar chewing pace) to control for confounding factors.

Standard balanced nutrients will be given for each meal during the second intervention period. Calories will be matched between groups for each meal and a total 24-h period within participants. Energy requirements for the day will be divided by sex calculated with the participants' average using the Harris-Benedict formula (29).

Males: resting metabolic rate (kcal/d) = 66.5 + (13.75 × weight in kilograms) + (5.003 × height in centimeters) − (6.775 × age in years);

Females: resting metabolic rate (kcal/d) = 665.1 + (9.563 × weight) + (1.850 × height) − (4.676 × age).

The energy allocation will be 30, 40, and 30% for breakfast, lunch, and dinner, respectively, with macronutrient ratios following the dietary guideline recommendations of 50–55% of calories from carbohydrates, 15–20% from protein, and 25–30% from fat. Daily meals will include vegetables, meat, and staple foods. After this trial, we will upload the realistic standard meals in the form of a photograph. The types of food are shown in Table 4.

**Table 4 T4:** Food types of standard meals.

**Food type**	**Staple food**	**Vegetable**	**Protein**
Breakfast	Noodles	Tomato	Egg
	Bread	Cucumber	Milk
	Rice	Cabbage	Pork
Lunch and dinner	Rice	Broccoli	Fish
		Cabbage	Chicken
		Carrot	Pork
		Mushroom	Egg
		Tomato	

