#### Interviews

Face-to-face interviews will be conducted at V4 to evaluate the participants' experiences and perceptions of the intervention in depth. All subjects will be invited to a personal semistructured interview of ~20 min to explore the feasibility and acceptability of the premeal snack intervention being included in their daily dietary habits. It will help to understand the feasibility of the intervention and the acceptability and sustainability of integrating this intervention into their daily lives. If subjects withdraw from this trial, they will be invited to record their reasons for withdrawing and their perceptions of the interventions by a face-to-face interview.

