### Comparisons

First, the three intervention arms will be combined as a group and compared with the control group to evaluate whether the premeal intervention could improve GV. Second, the two arms with high-protein snacks will be combined as a group and compared with the control group; moreover, the high-fat snack arm will be compared with the control group to evaluate whether the two snacks (high-protein and high-fat snacks) could improve GV. If both the high-protein and high-fat snacks show significant improvement effects, we will further directly compare the high-protein snack (combining milk powder and soy powder into one group) with the high-fat snack (almonds) interventions to evaluate which is better. Third, we will also compare the milk powder group with the control group and the soy powder group with the control group, and if both high-protein snack groups show significant improvement, we will further compare the animal protein and plant protein groups directly to verify whether the plant protein group is similar to the animal protein group. Finally, we will compare all the results from different dietary patterns to determine whether premeal snacks have similar effects under habitual diet and standard balanced meals.

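### Withdrawing participants for not consuming the study foods can, in the habitual-diet period, remove people only from the snack arms, which leaves the comparison with water open to selection bias of unknown size and direction

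*Protocol article*

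**What the plan says.** The protocol article gives two withdrawal criteria in Table 1: withdrawal of consent, and "Noncompliance with consuming the study foods". No threshold for noncompliance is given, and the term for the foods is not defined.

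Under Test snacks, the foods are soy powder, milk powder and almonds: "The specific composition of the three food items is shown in Table 3". For the fourth arm, "an equal amount of water (250 ml) will be given to subjects in the control group".

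Under Intervention, the first period (D3 to D6) runs on the participant's habitual diet. Supplied meals begin on D7: "Subjects will be given standard balanced meals 3 times per day during the run-in period". They continue from D10 to D13: "Standard balanced nutrients will be given for each meal during the second intervention period".

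For people who leave, the Interviews section provides one thing: "If subjects withdraw from this trial, they will be invited to record their reasons for withdrawing". It mentions no further outcome collection. Under Sample size determination, 6 per group is raised to 8 for 20% dropout, so dropouts count as lost to the analysis.

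Under Comparisons, the first analysis is that "the three intervention arms will be combined as a group and compared with the control group". Combined and single snack arms are then set against the same control. Participants and diet staff are not blinded.

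**The concern.** Whether someone eats the snack is known only after randomisation, and in the first period it can be judged only in arms that have a snack to eat. If failing to eat it ends participation, the people left in those arms are a selected group, while the control arm stays whole. The contrast then sets snack compliers against all controls, and randomisation no longer protects it.

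Three features of this trial sharpen the point. The staff who would notice noncompliance know the arm, and no threshold limits their judgement. With 8 per arm, one or two removals are a large fraction of a group. A removal in the first period also takes the person out of the second, so the imbalance carries over to the standard-meal results and to the comparison between the two diets.

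**Working it through.** **1. The plan's own figure.** Inputs from Sample size determination: 6 evaluable per group, 20% dropout. 6 / (1 − 0.20) = 7.5, rounded up to 8; 4 × 8 = 32. This reproduces. The 6 itself cannot be reproduced, because the article states no SD, margin or power. The allowance amounts to 0.20 × 8 = 1.6, that is 1 or 2 people per arm.

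**2. Who can meet the criterion, and when** (from Intervention, Test snacks, and Standard balanced meals run-in period).

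| Days | Supplied to snack arms | Supplied to control | Arms the rule can reach |
|---|---|---|---|
| D3–D6 | snack, with 250 ml water | 250 ml water | snack arms only |
| D7–D9 | standard meals | standard meals | all |
| D10–D13 | standard meals and snack | standard meals and water | all |

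Counting the control's water as a study food would not restore the balance in practice. The food diary leaves water out, so an undrunk glass would not show there, whereas a missed snack would.

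**3. How large the effect could be (assumptions, not figures from the article).** Take 8 per arm, no true effect and outcome SD 1. Remove the k least compliant people from each snack arm and none from control. Let rho be the correlation between compliance and a favourable glucose response.

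The expected distances from the mean of the two most extreme of 8 normal values are 1.424 and 0.852. The shift in a snack arm's mean is

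shift = rho × (sum of the k removed distances) / (8 − k)

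- k = 1: 1.424 / 7 = 0.203; × 0.3 = 0.06; × 0.5 = 0.10.
- k = 2: (1.424 + 0.852) / 6 = 0.379; × 0.3 = 0.11; × 0.5 = 0.19.

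A simulation of 60,000 runs with a two-sided t-test at 0.05 agrees, and adds the type I error:

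| rho | k | Shift (SD) | Type I error, three snack arms pooled vs water | Type I error, one snack arm vs water |
|---|---|---|---|---|
| 0 | 2 | 0.00 | 0.050 | 0.050 |
| 0.3 | 1 | 0.06 | 0.053 | 0.053 |
| 0.3 | 2 | 0.11 | 0.060 | 0.054 |
| 0.5 | 1 | 0.10 | 0.062 | 0.055 |
| 0.5 | 2 | 0.19 | 0.081 | 0.065 |
| 0.8 | 1 | 0.16 | 0.082 | 0.067 |
| 0.8 | 2 | 0.30 | 0.136 | 0.090 |

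With nobody removed (k = 0), the shift is zero and the type I error about 0.05 at every rho. If rho has the opposite sign, the shift has the same size and runs against the snacks.

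**4. Yardstick.** The standard error of a difference between two arms of 8 is √(1/8 + 1/8) = 0.5 SD. A shift of 0.19 SD is 0.19 / 0.5 = 0.38 of one standard error.

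**The case against.** **Direction.** A reader might infer that the comparison is biased in favour of the snacks. The article does not support that. Nothing in it links compliance to the change in MAGE or gives such a link a sign, and without a link the bias is zero. This objection stands: the rule opens a route to bias and does not establish one.

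**Size.** A reader might also take the 20% allowance as the expected number of snack refusals. It is a general dropout figure with no cause or arm attached. The article gives reasons to expect fewer: the snacks are common foods of 80 to 90 kcal given for 4 days per period, people with food allergy or gastrointestinal complaints are excluded, and diaries are supervised daily. Removing exactly the least compliant people, in snack arms only, puts the illustration near the upper end for a given rho. Even so, the shifts at rho 0.3 to 0.5 are well below one standard error. This also stands.

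**Reach.** It would be wrong to call the rule one-sided throughout. From D7 to D13, 7 of the 11 days from D3, controls can meet it too. The undefined term could be stretched to the control water, or to the common dinner before the experiment. The reference to three food items makes the narrower reading the natural one, but it is a reading.

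**Lost data.** The article does not say whether a withdrawn participant keeps the sensor, or whether glucose data already collected are used. One should not assert that readings are discarded while the sensor is still worn. Someone removed late in the first period may already have supplied much of D4 to D6, the days used for analysis. What the article does show is an interview and nothing more after withdrawal.

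**Scope and question asked.** Analysis sets are commonly left to a statistical analysis plan, and none is shown, so their absence is not the complaint. The complaint is the withdrawal rule, which the article does state; a later plan cannot recover outcomes that were never collected. An effect-if-eaten question is defensible for a trial of acute effects. It can still be answered from complete follow-up with intake recorded, but the as-randomised question cannot be answered once noncompliers have gone.

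**Non-inferiority.** Soy and milk face the same rule, so the asymmetry with water does not arise between them. Keeping noncompliers there can pull the two arms together and favour non-inferiority. This stands and shapes the fix.

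**Conclusion.** The point holds in a limited form. As written, the rule allows exclusion after randomisation that, from D3 to D6 and on the natural reading of the study foods, can fall only on the snack arms. Those excluded are missing from the second period as well. The snack-versus-water comparisons are left open to selection bias of unknown size and direction.

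The figures of 0.06 to 0.10 SD (1 of 8 removed per snack arm) and 0.11 to 0.19 SD (2 of 8) rest on an assumed correlation of 0.3 to 0.5, on removal confined to the snack arms, and on the least compliant being the ones removed. They point towards benefit only if noncompliers respond less well. In the most affected of these cases, the type I error of the pooled comparison is about 0.08 instead of 0.05. The effect is modest, but it can be avoided at little cost and should be corrected.

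**What to change.** - In Table 1, delete noncompliance as a reason to end data collection, so that stopping the snack is kept separate from leaving follow-up. Whether a noncompliant participant goes on receiving the snack is a separate matter for the investigators.
- Record snack intake daily in the existing food diary, and keep the sensor and visits V1 to V4 for everyone who still consents. Withdrawal of consent still ends data collection.
- Analyse the snack-versus-water comparisons in the arms as randomised, noncompliers included, with a complier (per-protocol) analysis as a sensitivity analysis.
- For soy versus milk, report the complier analysis alongside the as-randomised one, and read non-inferiority from both.

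The cost is one changed line in Table 1 and a short addition to the analysis plan. The sensor, the supervised diary and the visits are already scheduled, so no new procedure is needed. The drawback is that the as-randomised estimate is diluted by non-adherence: it describes the effect of offering the snack, and the complier analysis has to speak to the effect of eating it.

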### Randomization and allocation concealment

Stratified randomization will be used. Participants will be stratified by sex. Random number sequences will be generated using SPSS version 24.0 (SPSS Inc. Chicago, IL, USA). A researcher who is independent of the assessment of study outcomes and statistical analysis will perform the random assignments, and grouping code results will be placed in opaque envelopes to ensure group concealment. After inclusion is confirmed, the envelopes will be distributed in the order of inclusion, and the meaning of each group code will not be available to check the grouping status until the beginning of the study. Subjects and staff involved in diet management cannot be blinded, as the participants will consume easily identifiable snacks. Staff assessing clinical outcomes and conducting analysis will remain blinded to the allocation until the statistical analysis is completed.

### Intervention

This study consists of a baseline blood glucose assessment day (D2) under habitual diet conditions (before the start of the intervention, V1), two intervention periods under two different diet patterns with equal experimental days (D3-D6, D10-D13), and a standard balanced meal run-in period between the two intervention periods (D7-D9). A 3-day experiment run-in period will be set before Visit 1 (V1). During this period, all subjects will be asked to maintain their habitual eating without energy restrictions and maintain a regular daily schedule. In addition, they will not be allowed to smoke, drink, or perform vigorous exercise in the course of this trial. All subjects will wear continuous glucose monitoring (CGM) to monitor dynamic interstitial glucose in the mornings of V1. The first intervention period will be under the habitual diet condition from D3 to D6 (4 days), during which all subjects will be asked to maintain their habitual eating and daily activities, similar to the experimental run-in period. After the first intervention period, a 3-day standard balanced meal run-in period from D7 to D9 will be performed before the second intervention to ensure that the standard meals are tolerable to the individual participants. The second intervention will consist of prelunch snacks with standard meals that had the same macronutrient composition as those in the run-in period. Screening will be finished within 1 week before the experiment (V0). Randomization will be performed after the completion of screening. Outcomes will be assessed after the two intervention periods. Blood samples will be taken before and after the two intervention periods (V1-V4), and interstitial glucose will be monitored throughout the 2 week experimental period. An overview of the study visits is presented in Table 2. During the entire period of this experiment, subjects will be asked to complete a food recording diary (online) including the type, amount, and time of all meals, snacks, and drinks except water (in the form of photos and text). Subjects will be supervised daily by the researcher in charge to ensure their food diaries are uploaded on time. Physical activity and sleep will also be recorded via a mobile app for step count and sleep time records.

**Table 2 T2:** Overview of study visits.

**Visit**	**V0**	**V1**	**V2**	**V3**	**V4**
Time from the start of wearing CGM^a^	−7	1	7	10	14
**Participant information**					
Inclusion and exclusion criteria	X				
Informed consent	X				
Medical history (individual and family)	X				
**Outcomes**					
CGM^b^		X	X	X	X
Fasting blood samples		X	X	X	X
HbA1c	X				
VAS^c^	X				
Bodyweight		X	X	X	X
Waist and hip circumference	X	X	X	X	X
Food records^d^	X	X	X	X	X
Physical activity and sleep records	X				
**Questionnaires**					
Sociodemographic characteristics	X				
Eating habits	X				
Acceptability and compliance					X

a *CGM between 8:00 and 9:00 at Visit 1*;

b *collect CGM data from Visit 1 to Visit 4 for 14 consecutive days*;

c *at time points of 10 and 20 min after consumption of the snacks*;

d *records during the entire study*.

*CGM, continuous glucose monitoring; VAS: visual analog scale*.

### Test snacks

In the 3 premeal snack arms, all participants will be given prelunch snacks 30 min before lunch. Prelunch snacks will comprise soy powder and milk powder which will be completely dissolved in 250 ml of water, unsalted roast whole almonds snacks with 250 ml of water, while an equal amount of water (250 ml) will be given to subjects in the control group. The total calories of the three snacks will be similar to each other, from 80 to 90 kcal. This calorie selection was based on the minimum calories needed to relieve the symptoms of hypoglycemia (28). The specific composition of the three food items is shown in Table 3.

**Table 3 T3:** Macronutrient composition of the test snacks.

**Per serving**	**Soy powder**	**Milk powder**	**Almonds**
Weight(g)	18	25	13
Energy (kcal)	83	90	85
Carbohydrate (g, % of energy)	6.2 (30%)	14.0 (62%)	2.7 (12%)
Protein (g, % of energy)	7.2 (35%)	7.5 (33%)	2.7 (12%)
Fat (g, % of energy)	3.0 (32%)	0.38 (3%)	6.8 (72%)

*As an example for soy powder, in this trial, we used a total weight of 18 grams of soy powder as a pre-meal snack, which provided 83 kcal of total energy; of the 18 grams of soy flour, 6.2 g of carbohydrates provided 30% of the total energy, 7.2 g of protein provided 35% of the total energy, and 3.0 grams of lipids provided 32% of the total energy, respectively*.

### Standard balanced meals run-in period

A 3day run-in period will be scheduled between Visit 2 (V2) and Visit 3 (V3), during which subjects will be asked to maintain the same levels of rest and physical activity as they did during the experimental period. Subjects will be given standard balanced meals 3 times per day during the run-in period and will not be provided with premeal snacks. Furthermore, researchers will train the subjects to eat in the same fixed meal order and have a similar duration of each meal (to keep a similar chewing pace) to control for confounding factors.

Standard balanced nutrients will be given for each meal during the second intervention period. Calories will be matched between groups for each meal and a total 24-h period within participants. Energy requirements for the day will be divided by sex calculated with the participants' average using the Harris-Benedict formula (29).

Males: resting metabolic rate (kcal/d) = 66.5 + (13.75 × weight in kilograms) + (5.003 × height in centimeters) − (6.775 × age in years);

Females: resting metabolic rate (kcal/d) = 665.1 + (9.563 × weight) + (1.850 × height) − (4.676 × age).

The energy allocation will be 30, 40, and 30% for breakfast, lunch, and dinner, respectively, with macronutrient ratios following the dietary guideline recommendations of 50–55% of calories from carbohydrates, 15–20% from protein, and 25–30% from fat. Daily meals will include vegetables, meat, and staple foods. After this trial, we will upload the realistic standard meals in the form of a photograph. The types of food are shown in Table 4.

**Table 4 T4:** Food types of standard meals.

**Food type**	**Staple food**	**Vegetable**	**Protein**
Breakfast	Noodles	Tomato	Egg
	Bread	Cucumber	Milk
	Rice	Cabbage	Pork
Lunch and dinner	Rice	Broccoli	Fish
		Cabbage	Chicken
		Carrot	Pork
		Mushroom	Egg
		Tomato	

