**Inclusion criteria**
• Aged from 18 to 60 years • FBG 6.1–6.9 mmol/L (IFG) OR 2 h PG (75 g OGTT) 7.8–11.0 mmol/L (IGT) OR HbA1c 5.7–6.4% • Stable bodyweight (changes <5 kg) in the past 3 months • Consumes 3 meals (breakfast, lunch, and dinner) a day at regular time points • Similar levels of physical activity (light manual worker)

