Another important advantage of the trial is that we will implement a premeal snack intervention under two different dietary conditions. Several studies have reported the beneficial effects of premeal snack interventions on glucose metabolism under well-controlled dietary patterns (14, 40, 42). Although the effects observed in this way are significant, such studies under well-controlled conditions could not represent the full extent of this benefit in real daily diet because GV itself can vary with the order of meals, macronutrient ratios, and the interval between meals (11). The purpose of this design is to determine whether the intervention, when applied to a daily diet, will result in improvements similar to those obtained under the experimental control diet. First, before the start of the experiment, we will set a run-in period with the aim of testing the baseline GV levels of the subjects as their own control. After the run-in period, the first period of the intervention will begin, and premeal snacks will be given under exactly the same habitual diet conditions as those in the run-in period, during which no restrictions will be imposed on the amount and type of food consumed by the subjects at their regular meals. After the end of the first intervention period, a standard balanced meal run-in period will be set to ensure that the subjects' metabolism adapts to this meal pattern before the start of the second intervention period, to obtain more stable data for the second-period results.

Notably, as the prediabetic population continues to expand, the solution to reduce the risk of the development of diabetes in this population is an urgent issue. It has been reported that in the process of disorders in glucose metabolism, the increase in postprandial glucose excursion and delayed duration of postprandial glucose excursion occurs earlier than the increase in FBG levels in patients with prediabetes (43). Our study will select subjects from the pre-diabetic population aim to alleviate glucose metabolism and achieve prevention through simple and easily implemented lifestyle interventions. In addition, the results from the prediabetic population are more likely to be extrapolated to diabetic populations.

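### As printed, the standard meals supply only resting energy: an avoidable confounder of the habitual-versus-standard diet comparison

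*Protocol article*

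**What the plan says.** The energy rule is in the Protocol article, section Standard balanced meals run-in period: "Energy requirements for the day will be divided by sex calculated with the participants' average using the Harris-Benedict formula". One equation per sex follows. The male one opens "Males: resting metabolic rate (kcal/d) = 66.5", and the female one carries the same resting-rate label. The text then divides the daily total 30/40/30% over breakfast, lunch and dinner and gives macronutrient ranges. No activity multiplier appears there or elsewhere in the article, and no kcal total is printed. Calories are to be matched across arms.

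On activity, Table 1 requires "Similar levels of physical activity (light manual worker", together with body weight stable to within 5 kg over three months. During the D7-D9 run-in, participants are to "maintain the same levels of rest and physical activity as they did during the experimental period".

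On the other diet condition, the Intervention section has participants "maintain their habitual eating without energy restrictions and maintain a regular daily schedule" in the first run-in. Period 1 (D3-D6) continues in the same way, and the Discussion calls it ad libitum. Period 2 (D10-D13) uses "standard meals that had the same macronutrient composition as those in the run-in period".

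The last planned step under Comparisons is to "determine whether premeal snacks have similar effects under habitual diet and standard balanced meals". The Discussion asks whether snacks added to an everyday diet "will result in improvements similar to those obtained under the experimental control diet" and lists the contrast of dietary patterns as the third of three study questions. It also says that leftovers are recorded so that energy-intake differences can be ruled out as a cause of changes in glycemic variability (GV).

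**The concern.** Resting rate is what the body spends at rest. The daily requirement of someone who works is that amount plus the cost of activity. The article calls its result a daily requirement but calculates a resting rate, and no printed step leads from one to the other. Anyone who follows the rule as written underfeeds weight-stable light manual workers.

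What is at stake is the reading of the third study question. Each period has its own baseline (D2, D9) and a water control, so a GV shift common to all arms largely cancels. A change in the snack effect itself does not cancel, and that change is what the cross-period comparison examines. If the snack effect differs between periods, lower energy in period 2 is one possible reason. This works against the protocol's stated wish to exclude energy differences.

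**Working it through.** The article prints no kcal figure for the standard meals, so there is none to reproduce. The check evaluates the printed equations and compares the result with expenditure.

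**Inputs from the article:** the two resting-rate equations, the 40% lunch share and the 80-90 kcal snack.

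**Assumptions, not in the article:** activity factor (AF) 1.2 to 1.4; a man of 72 kg and 170 cm and a woman of 60 kg and 160 cm, both aged 40.

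**Step 1, relative shortfall.** If expenditure = resting rate × AF and intake = resting rate, then shortfall = 1 − 1/AF. Body size drops out.
- AF 1.2: 1 − 1/1.2 = 16.7%
- AF 1.4: 1 − 1/1.4 = 28.6%

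The direction needs no assumed value: any AF above 1 gives a deficit.

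**Step 2, printed rule for the illustrative bodies.**
- Man: 66.5 + 13.75×72 + 5.003×170 − 6.775×40 = 66.5 + 990 + 850.5 − 271 = 1,636 kcal/d
- Woman: 665.1 + 9.563×60 + 1.850×160 − 4.676×40 = 665.1 + 573.8 + 296 − 187.0 = 1,348 kcal/d

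**Step 3, daily and lunch energy (lunch = 0.4 × daily).**

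| | As printed | AF 1.2 | AF 1.4 |
|---|---|---|---|
| Man, kcal/d | 1,636 | 1,963 | 2,290 |
| Man, lunch kcal | 654 | 785 | 916 |
| Woman, kcal/d | 1,348 | 1,617 | 1,887 |
| Woman, lunch kcal | 539 | 647 | 755 |

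**Step 4, snack relative to lunch.** The snack stays fixed while lunch shrinks. Taking 85 kcal, the middle of the stated range:
- Man: 85/654 = 13% as printed, against 85/916 = 9% at AF 1.4
- Woman: 85/539 = 16% as printed, against 85/755 = 11% at AF 1.4

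A different snack effect from energy alone is therefore plausible. Its size cannot be derived from the article.

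These figures set the printed rule against assumed expenditure, not against period-1 intake, which the article does not give.

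**The case against.** **The article is condensed.** It names the target as the day's requirement and cites a source for the formula, so a multiplier may have been applied and left out of print. That stands: nothing shows what was or will be served. It is not a full answer, because the article prints the coefficients, the meal split and the macronutrient ranges. The rule is stated, and as stated it gives the wrong quantity.

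**The cross-period contrast is a bundle by design.** This also stands. A reader might infer that the missing factor is what prevents diet pattern from being separated from energy restriction, and that supplying it would restore a clean comparison. The document does not support that. The habitual diet always comes first, the standard meals fix macronutrient ratios, and participants are trained in meal order and pace. All of these differ between periods and would remain after the change.

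**Diaries and leftovers are recorded in both periods.** They would show an energy gap. They cannot remove it, because everyone receives formula-set energy in period 2.

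**The energy rule may not cover D7-D9.** The link between run-in and period-2 meals concerns macronutrient composition, not energy, and the calorie rule follows a sentence about the second intervention period. The extension to D7-D9 is therefore conditional.

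**Conclusion.** The point holds for the rule as printed. It equates a daily requirement with a resting rate, so the period-2 meals would fall about 17-29% below expenditure at assumed factors of 1.2-1.4. A larger factor would give a larger shortfall, but the article states none. The deficit adds an avoidable confounder to a comparison that already has several.

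A reader might go further and infer that the snack-versus-water results or the MAGE primary outcome are biased. They are not: arms are randomised, receive matched calories and are compared within a period against a water control. The sample size does not use the meal energy at all. Nor does the article establish that participants eat less in period 2 than in period 1. Stable weight suggests that habitual intake is near expenditure, but the tolerance is 5 kg and no intake is given. No bias in the snack effect has been quantified. The correction is worthwhile but does not affect the core of the trial.

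**What to change.** State that daily energy equals the mean Harris-Benedict resting rate for that sex multiplied by one stated light-activity factor, split 30/40/30, and print the resulting kcal/d for men and women. With the illustrative bodies and a factor of 1.4, this is 2,290 kcal/d for men (lunch 916) and 1,887 for women (lunch 755). Say whether the rule also governs D7-D9. One figure per sex keeps the arms matched. If a factor was already used, printing it is enough.

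The cost is more food: 40% more meal energy than the printed rule at a factor of 1.4. No visits or measurements are added. One factor per sex will fit some individuals poorly and will not equal each person's habitual intake.

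The article describes recruitment in the past tense, so a menu change may come too late. If meals were or must be served at resting rate, describe them as energy-reduced, report diary energy for both periods, and word the cross-period conclusion as habitual diet versus energy-reduced standard meals. That costs only wording and a table from data already collected.
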